#### Comparative evaluation

 The primary outcome measure for the *comparative evaluation* is independence in activities of daily living, assessed with the Barthel Index (BI) at admission to the GR facility and within two weeks post-GR, after completion of the GR trajectory. For both the Better@Home cohort and historical control group, the BI scores at admission are retrieved from the electronic patient files (EPF). The post-GR scores of the BI for the historical control group are also retrieved from the EPF. This data is routinely gathered by healthcare professionals of the participating GR facilities and stored in the EPF, most commonly in the Clinimetric Measurements tab. However, the post-GR scores of the BI for the Better@Home cohort are assessed by trained research assistants within 2 weeks of discharge. This is due to local GR protocols in which GR facilities do not routinely assess the BI after completion of home-based GR.

The BI, initially described by Mahoney and Barthel, is a 10-item measure of activities of daily living used in clinical practice to assess baseline abilities, quantify functional change after rehabilitation, and inform discharge planning. It comprises ten items: feeding, toilet use, bathing, grooming, dressing, bowel and bladder control, chair transfers, stair climbing, and ambulating [21]. In clinical practice, the patients are rated based on their medical records or direct observation. In a research setting, the patient is questioned during a face-to-face interview. Patients are rated on whether they can perform tasks independently, with assistance, or require assistance. The scoring on the modified version of the BI used in the present study ranges from 0 to 20. Higher scores indicate greater independence [21]. The BI’s structural validity, reliability, and interpretability are sufficient for measuring and interpreting changes in the physical function of geriatric rehabilitation patients [21–23].

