#### Comparative evaluation

 In the cost-effectiveness analysis, effects on the independence in daily functioning (BI) and healthcare-, patient & family costs are compared between the Better@Home cohort and historical control group at admission to GR and at post-GR, after completion of the GR-trajectory.

Healthcare costs are divided into costs made during inpatient GR and home-based GR. Healthcare costs during inpatient GR consist of the length of stay in the GR facility and (re)admissions to the hospital. This data can be accurately collected from the EPF in both the Better@Home cohort and historical control group. Healthcare costs during home-based GR consist of consultations with care professionals as well as additional healthcare costs. Consultations with care professionals (i.e., physical therapists, occupational therapists, dietitians, speech therapists, physicians, psychologists, nurses, and others) during home-based GR are registered on registration forms by the care professionals and include treatment volume, treatment time, and travel time. Furthermore, the nature of these consultations (at home, outpatient, or remotely using eHealth) is also registered by the care professionals. Additional healthcare costs during home-based GR are collected in a face-to-face interview with the patient after completion of the GR trajectory and include home care, domestic care, hospital care (both inpatient and outpatient), and general practitioner consultations. No data on healthcare costs during home-based GR was gathered for the historical control group, as this was an exclusion criterion.

Regarding patient and family costs during inpatient GR, the costs of informal care are assessed by multiplying an estimated volume of informal care provided during inpatient GR with a standardized reference price per hour [36, 37] in both cohorts. In addition, patient and family costs during home-based GR consist of the volume of informal care received by the patient, which is assessed during the face-to-face interview with the patient post-GR. Travel expenses are calculated by multiplying the number of visits to a healthcare service with standardized distances and transportation prices, including parking fees. Both standard distances and transportation prices are provided by the manual for cost research and reference prices [36, 37].

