#### Mixed-methods feasibility study

The feasibility study is conducted with a mixed method approach. It assesses the feasibility of the Better@Home program, as perceived by patients in the Better@Home cohort, their primary informal caregivers, and care professionals involved in their GR treatment. Feasibility is operationalized according to the method of Saunders [38], focusing on the following aspects: performance of the program according to plan, including the extent to which all core elements of the program were provided to the target population (fidelity and dose delivered completeness); extent to which the intended target group for the pathway was reached (reach); the extent to which the patients and informal caregivers actively engaged in the program (dose received exposure); barriers and facilitators that may have influenced the implementation of the program (context); and overall opinion of patients, informal caregivers and care professionals with the program (dose received satisfaction).

Data is collected among the patients of the Better@Home cohort using face-to-face structured interviews and among the informal caregivers using self-administered questionnaires. These structured interviews and questionnaires are administered at admission to GR, after completion of the GR trajectory, and after three months of follow-up. Data among the care professionals are gathered using registration forms, which the care professionals administer after providing home-based therapy and during or after weekly multidisciplinary team meetings. In addition, semi-structured group interviews (one group interview per GR facility) are conducted about two months after the inclusion of new patients in the study is closed. The group interviews are conducted with multidisciplinary project group representatives who led the Better@Home implementation in the eight participating GR facilities. Table 3 presents the data collected for the mixed-methods feasibility study.

**Table 3 Tab3:** Data collection mixed-methods feasibility study Better@Home cohort

Process domain/indicators	Operalization	Admission GR	Post GR	Follow-up 3 months	2 months after closing inclusion
**Reach** Extent to which the intended target group for the pathway was reached	The number who refused, dropped out or completed the pathway.	RF	RR	RR	
	Reasons for refusals and dropouts	RF	RR	RR	GI

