### Data analysis

#### Outcome assessment

Statistical analyses will be performed using the statistical software package IBM SPSS Statistics. For both the *comparative evaluation* and the *follow-up evaluation*, descriptive statistics will be used to describe the background characteristics and scores on the outcome measures at admission to the GR facility of patients and informal caregivers (only in the Better@Home cohort). Furthermore, model assumptions (e.g. normality, linearity) will be checked for each model. If a model assumption is violated, appropriate remedies are considered. Missing data on the outcome variables will be addressed by using mixed models, with missing data on the covariates being addressed by using multiple imputation if the percentage of missing values is more than 5%. Both mixed models and multiple imputation yield unbiased and efficient estimates under the missing at random (MAR) assumption. Lastly, the analysis models for both the *comparative* and *follow-up* evaluations adjust for GR facility using dummy coding, which corresponds to a fixed-effects approach. This method fully accounts for between-center variability [41]. Within-center variability is addressed by adjusting for individual-level characteristics in the models, including age, sex, living situation, and diagnosis. Additionally, frequency matching between the Better@Home cohort and historical control group helps to further the balance. However, while confounding at the center level is not an issue thanks to a fixed-effect approach, we cannot be certain that some relevant confounder is omitted at the subject-level.

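### Hospital care in the home-based phase is recorded only by a patient interview after completion of GR, so these costs may be missing for Better@Home patients who die or cannot be interviewed

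*Protocol article*

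**What the plan says.** The cost part of the comparative evaluation (Data collection, Cost assessment) names its sources by phase.

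- Inpatient phase: "Healthcare costs during inpatient GR consist of the length of stay in the GR facility and (re)admissions to the hospital". Of these items the article says: "This data can be accurately collected from the EPF in both the Better@Home cohort and historical control group".
- Home-based phase: "Additional healthcare costs during home-based GR are collected in a face-to-face interview with the patient after completion of the GR trajectory". The items listed "include home care, domestic care, hospital care (both inpatient and outpatient), and general practitioner consultations". Consultations with GR professionals in this phase come from registration forms instead.
- Controls: "No data on healthcare costs during home-based GR was gathered for the historical control group, as this was an exclusion criterion". Every admission counted for a control is therefore read from the EPF.

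The Barthel Index (BI) is the effect measure in the cost-effectiveness ratio. Here "the post-GR scores of the BI for the Better@Home cohort are assessed by trained research assistants within 2 weeks of discharge", while control scores come from the EPF.

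On missing values, the Data analysis section states: "Missing data on the outcome variables will be addressed by using mixed models". Covariates are multiply imputed, and both methods are justified under missing at random (MAR). For costs, a complete case analysis is listed among the sensitivity analyses. For Better@Home only, Table 3 records "The number who refused, dropped out or completed the pathway", together with reasons, as feasibility data on reach.

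**The concern.** Readmission soon after going home is a foreseeable cost of a programme that aims to replace 5 to 7 inpatient days with rehabilitation at home. In that phase the article relies on the patient's own later account for hospital care. This source works worst for the patients with the most serious events: those who die give no account, and those in hospital or too ill may give none.

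The stake is the cost conclusion. If Better@Home turns out cheaper with similar outcomes, the analysis plan moves to cost-minimization, and the conclusion then rests on the cost difference alone. A gap in hospital costs for the sickest patients at home lies inside that difference. The same patients are likely to lack a post-GR BI, so the effect side is exposed as well, although there the problem can arise in both groups.

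**Working it through.** **Step 1. Sources side by side** (Cost assessment and Outcome assessment, both under Data collection)

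| Item | Better@Home | Control |
|---|---|---|
| Inpatient GR: stay and hospital admissions | EPF | EPF |
| Home phase: hospital care, home care, GP | patient interview after completion | no such phase |
| Home phase: GR consultations | registration forms | no such phase |
| Post-GR BI | research assistant | EPF |

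The difference in source follows the phase of care. It affects one group because only that group has the second phase.

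**Step 2. What each source can see**

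- Admission during inpatient GR, either group: in the EPF, so counted.
- Home-phase admission, patient later interviewed: counted by self-report.
- Home-phase admission, patient dies: no interview, and no other source named.
- Home-phase admission, patient does not return or is too ill: possibly no interview.

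In the last two cases the inpatient length of stay and the registered consultations remain on record. The interview-based component is what is lost.

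**Step 3. Whether the stated analysis recovers it**

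A MAR method fills the gap from interviewed patients with similar covariates; death or a non-returning admission plausibly breaks that assumption. A complete case analysis omits the same patients. The dropout reasons would identify many of them, but they sit under feasibility with no stated link to costs. For a patient who died, a mixed model under MAR also implies a post-GR BI that never existed.

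**Step 4. Precision is not the issue**

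The plan's design figures are d = 0.51 (120:120) and d = 0.45 (120:240), with 80% power, two-sided 5% and a variance inflation factor of 2.

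d = (1.960 + 0.842) x sqrt(2 x (1/n1 + 1/n2))

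- 120:120: 2.802 x sqrt(0.03333) = 0.51
- 120:240: 2.802 x sqrt(0.02500) = 0.44 (power at the stated 0.45 is 81%)

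Both reproduce within rounding. If 5% or 10% of the 120 are lost (114:240 or 108:240), the second becomes 0.451 or 0.459. The loss matters through bias, hardly through power.

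**Step 5. Possible size, by assumption only**

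The article gives no rate of death, readmission or non-interview, and no unit costs.

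(a) Patients kept in the analysis with the hospital component counted as nil. Assume a share p of 5-10% (6 to 12 of 120), 7 hospital days each, and a price k of 1-2 GR days per hospital day. The omitted cost per enrolled patient is p x 7 x k:

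- low: 0.05 x 7 x 1 = 0.35 GR-day equivalents
- high: 0.10 x 7 x 2 = 1.4 GR-day equivalents

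Against the target reduction of 5 to 7 inpatient days this is 0.35/7 = 5% to 1.4/5 = 28%. The target counts inpatient days and is not a net saving.

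(b) Patients left out of the cost mean altogether. With a share q left out, whose true mean cost is r times that of the others, the mean is understated by q(r-1)/(1+q(r-1)):

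| q | r = 0.5 | r = 1.5 | r = 2 | r = 3 |
|---|---|---|---|---|
| 5% | -2.6% | 2.4% | 4.8% | 9.1% |
| 10% | -5.3% | 4.8% | 9.1% | 16.7% |

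A negative entry means the mean is overstated, for example when early deaths have short and cheap trajectories.

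**The case against.** The strongest reply is that the article condenses a fuller document, so a proxy interview, a record fallback or the base-case rule for missing costs may be written there. That is fair for the imputation rule, and its absence is not the point here. The interview as the source for home-phase hospital care is stated, and its blind spot for patients who die follows from the statement itself. An interview is also a reasonable choice if GR files record hospital stays after the move home poorly, which is a reason to keep it as a second source.

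A reader might infer more than the article supports:

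- *Deaths and readmissions vanish from the Better@Home group only.* Its inpatient-phase admissions are read from the EPF just as in controls, and nothing says that patients without an interview are excluded. Complete case analysis is named only as a sensitivity analysis.
- *Non-completers are never interviewed.* The article times the post-GR measurement both by completion of the trajectory and by discharge, and does not define completion so as to rule out a trajectory that ended early. Only deaths and patients unable to be interviewed are clearly lost.
- *Post-GR BI is missing in one group only.* A control who died or was transferred may equally have no post-GR score in the EPF.
- *All the bias favours Better@Home.* Omitted admissions do lower its hospital component, but part (b) of the working shows that the effect on mean cost can take either sign. Better@Home also carries home-phase costs with no control counterpart, which pushes the difference the other way.
- *5% to 28% is an estimate.* Only the 5 to 7 days come from the article.

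The article does concede residual confounding, selection bias and limited internal validity. Its limitations do not mention this data source.

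**Conclusion.** The point holds as a phase-specific gap in data capture. In the home-based phase, Better@Home hospital care is recorded solely by a patient interview after completion, while all other admissions in the comparison come from the EPF. Home-phase hospital costs of patients who die, or who are readmitted and cannot be interviewed, may be missing, and neither the MAR methods nor the complete case analysis recovers them.

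The direction is clear for one component: omitted admissions understate Better@Home hospital costs. For the mean cost difference, both direction and size depend on unstated rates and unit costs; the ranges in the working are illustrations. Missing post-GR BI is a shared problem of both groups and plausibly not MAR. The matter should be settled before the cost comparison is reported, since a cost-minimization conclusion would rest on it.

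**What to change.** 1. In the cost part of the comparative evaluation, take hospital admissions and deaths up to the end of the GR trajectory from the GR file for every enrolled Better@Home patient, completed or not. Supplement this with whatever the registration forms and the researchers' dropout reasons already hold.
2. Keep the interview as a supplementary source for hospital care, and as the source for home care, domestic care and GP contacts.
3. For both groups, extract from the EPF the reason for a missing post-GR BI (death, hospital transfer, long-term care, other).
4. Report death, hospital admission and non-completion by group beside the BI and cost results.
5. Add a sensitivity analysis for costs and BI that departs from MAR for non-interviewed patients, for example by giving them a range of higher and lower costs and lower BI values.

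Cost: a few extra fields from files the facilities already use, and some added wording. Control data reach the researchers anonymised, so item 3 needs a further request to the facilities. The registration forms are described as recording consultations, so they may add little on admissions. Some home-phase admissions will still be poorly recorded in the GR file. Since the article expects data collection to end in April 2025, the file extraction would be retrospective.

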## Methods

### Study design

The Better@Home study is a cohort study accompanied by a mixed-methods feasibility study (Fig. 1). The Better@Home study includes an outcome assessment to assess the program’s outcomes and a cost assessment to assess the costs in relation to the outcomes. Within the cohort study, two evaluations can be distinguished: [1] a *comparative evaluation*, to assess the outcomes and costs from admission to completion of GR in the prospective Better@Home cohort receiving the Better@Home program, compared to a historical control group who received usual care; [2] a *follow-up evaluation*, to assess the course of the outcomes and costs solely within the prospective Better@Home cohort, from admission to three months post-GR. The *mixed-methods study* is to assess the feasibility of the Better@Home program, from admission to three months post-GR. The mixed-methods study incorporates both quantitative and qualitative methods. It evaluates the program’s reach, performance according to plan, active engagement of patients and informal caregivers, barriers and facilitators affecting implementation, and the opinions of patients, informal caregivers, and professionals on the program.

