The matched historical control group represents patients who received usual care. This cohort consists of patients admitted to the participating GR facilities between January 2022 and June 2023—at least six months before the implementation of the Better@Home program—thereby minimizing contamination bias while ensuring a similar context of care. Furthermore, in order to maintain the integrity of the comparison, patients who received home-based GR prior to the implementation of Better@Home program will be excluded from the matched historical control group. Several participating GR facilities already offered home-based GR during the comparison period; including these patients could lead to contamination of the usual care group and an underestimation of the Better@Home program’s effects.

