#### *Follow-up evaluation* 

A cost analysis is performed in the *follow-up* evaluation which assesses the course of costs in the Better@Home cohort from GR admission up to three months post-GR. In addition to the costs assessed during inpatient and home-based GR, the healthcare-, family & patient costs made during the three months of follow-up are assessed by a face-to-face interview with the patient. These costs include home care, domestic care, hospital care (inpatient and outpatient), general practitioner consultations, mental healthcare utilization, utilization of allied care professionals, use of assistive devices, and informal care utilization.

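### Costing runs to the end of home-based GR for Better@Home but in effect only to inpatient discharge for controls, so care at home over the excess days is counted in one group only

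*Protocol article*

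**What the plan says.** The Study design section sets the aim of the comparative evaluation as "to assess the outcomes and costs from admission to completion of GR in the prospective Better@Home cohort" against a historical usual-care group. The end point is therefore an event, the end of GR, and not a common time from admission. Under Setting and population, "patients who received home-based GR prior to the implementation of Better@Home program will be excluded from the matched historical control group".

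The Cost assessment (Data collection, Comparative evaluation) then lists what is counted.

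- **Both groups, healthcare:** "Healthcare costs during inpatient GR consist of the length of stay in the GR facility and (re)admissions to the hospital".
- **Both groups, informal care:** a reference price applied to "an estimated volume of informal care provided during inpatient GR".
- **Better@Home only, GR contacts:** consultations with GR professionals in the home phase.
- **Better@Home only, other care:** additional healthcare costs, which "include home care, domestic care, hospital care (both inpatient and outpatient), and general practitioner consultations".
- **Better@Home only, informal care at home:** "patient and family costs during home-based GR consist of the volume of informal care received by the patient".

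For controls, "No data on healthcare costs during home-based GR was gathered for the historical control group, as this was an exclusion criterion".

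Table 1 gives a target of 5 to 7 inpatient days replaced on average and leaves the length of the home phase open. The perspective is societal. The named sensitivity analyses (Data analysis, Cost assessment) are a complete-case analysis and a healthcare-perspective analysis.

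**The concern.** Having had no home-based GR is a sound reason for recording zero home GR sessions in controls. It is no reason to record zero home care, domestic help, GP use or informal care for an older person who has just gone home. Those costs fall outside the control window only because that window closes at discharge.

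The programme itself moves the closing date in the other group. Where the home phase outlasts the inpatient days it replaces, ordinary costs of living at home are attributed to Better@Home and have no counterpart among controls.

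The incremental cost feeds the ICER and the bootstrap quadrants. The Data analysis section also picks the type of analysis partly by the sign of the cost difference: cost-minimization if there are savings with comparable outcomes, an ICER if incremental costs and outcomes are both positive. A distortion in cost could therefore shift the estimate and also select the method.

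**Working it through.** The protocol states no cost figure or home-phase length, so there is no published number to reproduce. The check is structural, followed by an illustration on stated assumptions.

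**1. Window lengths.** Let L be the control inpatient stay, S the inpatient days replaced and H the days of home-based GR.

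- Control window = L
- Better@Home window = (L − S) + H
- Difference = H − S

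That the control window ends at discharge is inferred from the exclusion rule and the listed cost items; it is not stated outright.

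**2. What is artefact and what is real.** On the S replaced days a control is still in a costed bed. Care at home for a Better@Home patient on those days is a genuine cost of substitution. Only the H − S excess days are unmatched. With c the daily cost of community and informal care that a discharged control would also incur:

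- Artefact ≈ c × (H − S)

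**3. Inputs.** S = 5 to 7 (Table 1, a target). Assumed, because the protocol gives no value:

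- H = 14 or 28 days
- c = 1 to 2 hours per day at EUR 20 to 60 per hour, so 1 × 20 = EUR 20 to 2 × 60 = EUR 120 per day
- Inpatient day price b = EUR 300 to 400, so the gross saving S × b runs from 5 × 300 = EUR 1,500 to 7 × 400 = EUR 2,800

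**4. Results per patient.**

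| H | S | H − S | Artefact (EUR) | Gross saving (EUR) |
|---|---|---|---|---|
| 28 | 5 | 23 | 23 × 20 = 460 to 23 × 120 = 2,760 | 1,500 to 2,000 |
| 28 | 7 | 21 | 21 × 20 = 420 to 21 × 120 = 2,520 | 2,100 to 2,800 |
| 14 | 5 | 9 | 9 × 20 = 180 to 9 × 120 = 1,080 | 1,500 to 2,000 |
| 14 | 7 | 7 | 7 × 20 = 140 to 7 × 120 = 840 | 2,100 to 2,800 |

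**5. Where the artefact alone exceeds the gross saving.** This needs c > S × b / (H − S). At H = 28:

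- S = 5, b = 300: c > 1,500 / 23 ≈ EUR 65 per day
- S = 5, b = 400: c > 2,000 / 23 ≈ EUR 87 per day
- S = 7, b = 300: c > 2,100 / 21 = EUR 100 per day
- S = 7, b = 400: c > 2,800 / 21 ≈ EUR 133 per day, outside the assumed range

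At H = 14 it does not happen anywhere in the assumed range.

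**6. Boundary cases.** At H = S the term is zero. At H = 5, S = 7 it is −2 days: Better@Home patients finish GR before controls would be discharged, and the distortion then favours the programme.

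The saving here is gross. Home GR contacts and genuine care on the replaced days also reduce it, so the net margin is smaller by an amount that the protocol does not allow one to compute.

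**The case against.** The strongest defence is that the horizon is a declared episode of care, applied to both costs and the Barthel Index. The Discussion discloses that no control data exist after GR ends. The analysis is described as exploratory, the list of sensitivity analyses is a minimum, and the healthcare perspective removes the informal-care part. If the home phase does outlast the days replaced, the planned base case errs against the programme, so a saving found despite it would stand.

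Part of this holds. An episode horizon is legitimate, and the conservative direction helps when H > S and a saving is found. The rest does not close the gap. An episode end point that the intervention itself shifts does not give equal windows. The Discussion draws the consequence of the missing control data only for long-term conclusions from the follow-up evaluation, not for this comparison. The healthcare perspective still keeps home, domestic, GP and hospital care on one side only.

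A reader might go further in three ways that the document does not support.

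- **All home-phase care is artefact.** It is not; the S replaced days carry real shifted cost.
- **The artefact always runs against Better@Home and is as large as the saving.** The direction depends on H relative to S, and the size depends on inputs that the protocol does not give.
- **The base case should be cut to items available in both groups.** That would credit the saved bed-days without charging for care passed to home-care services and families, biasing the result towards Better@Home.

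**Conclusion.** The windows are unequal by H − S days, and ordinary community and informal care over those days is counted for Better@Home only. When H > S the incremental cost of Better@Home is overstated; when H = S there is no distortion; when H < S it is understated. With an assumed 28-day home phase the artefact is about EUR 420 to 2,760 per patient, against an assumed gross saving of EUR 1,500 to 2,800, so it may change the sign of the cost difference in part of that range. With 14 days it stays below the gross saving. The structure follows from the protocol, given the inference that control GR ends at inpatient discharge. The euro amounts rest wholly on assumed home-phase length, hours and prices, so a reversed cost conclusion is a possibility and not a demonstrated result. No common-window analysis is named that would show which case applies.

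**What to change.** Keep the planned societal base case and add to it.

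1. **Prespecify an equal-horizon scenario.** Give controls a per-day community and informal-care cost from discharge to a common time from admission, for example the mean Better@Home trajectory length in the same facility and diagnosis/Barthel stratum. Frequency matching gives no paired patient, so a stratum mean is needed. With 120 patients planned over eight facilities (120 / 8 = 15 each on average), a rule for pooling thin strata should be stated.
2. **Take the per-day cost from data already collected.** Use the Better@Home home phase or the follow-up period, in which "the healthcare-, family & patient costs made during the three months of follow-up are assessed by a face-to-face interview with the patient". Restrict it to the item types in the comparative home-phase list, since the follow-up also covers mental healthcare, allied care and assistive devices. Vary it from 50% to 150%.
3. **Report the one-sided home-phase items separately**, with the observed H and S, so that readers can see the excess window.
4. **State the unequal window as a limitation** of the cost comparison, the ICER and the choice of cost-minimization.

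The cost is extra analysis and reporting; no new data collection is needed. The downside is that the scenario rests on a stated assumption about control costs after discharge, borrowed from patients who may have been selected partly on the availability of home and informal care (Setting and population).
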